## Abstract

**Background:**

About three-quarters of people with dementia live in their own homes, with help from family members and/or other unpaid carers, such as friends or neighbors. Often, unpaid carers themselves experience negative consequences, such as stress, burden, and symptoms of depression or anxiety. Research has shown that these consequences can be alleviated by psychosocial and psychological interventions. Moreover, there are indications that those interventions can be effective when offered online.

**Objective:**

This paper describes the protocol of a randomized controlled trial (RCT) that will take place in the Netherlands to evaluate the effectiveness of iSupport, a minimally guided, internet-based intervention to improve carers’ mental health and coping resources.

**Methods:**

A superiority two-arm RCT comparing the effects of the online support program with a waiting list control condition will be carried out in the Netherlands. The iSupport intervention was developed by the World Health Organization and is based on cognitive behavioral therapy principles. It has five main themes divided into 23 lessons. Carers can pick and choose which lessons they want to complete. We aim to recruit 200 unpaid carers. The experimental group (n=100) will be provided with access to the intervention for 3 months following randomization; those in the waiting list control group (n=100) will be granted access to the intervention after 3 months. Assessments will be conducted at baseline (T0), 3 months after baseline (post intervention, T1), and 6 months after baseline (follow-up, T2). The primary outcome is perceived stress, measured by the Perceived Stress Scale. Secondary outcomes are symptoms of depression and anxiety, caregiver burden, sense of competence, self-efficacy, mastery, and carers’ attitudes toward dementia and their person-centered approach (ie, to what extent carers tailor the provided care to the interest, needs, and history of the person with dementia).

**Results:**

Recruitment for the trial started in January 2019. As of July 2019, we have enrolled 120 participants. 
Data collection is expected to be completed by March 2020. Once all the data have been collected, we will conduct the data analyses between April and May 2020. We aim to publish our results in a manuscript by June 2020.

**Conclusions:**

Online interventions have shown promising results in improving the mental health of carers of people with dementia. Additionally, online interventions may overcome accessibility barriers. If successful, this intervention will have important potential for implementation as a public health intervention, since costs and support by trained staff are minimal.

**Trial Registration:**

Netherlands Trial Register (NTL) NL6417; https://www.trialregister.nl/trial/6417

**International Registered Report Identifier (IRRID):**

DERR1-10.2196/14106

## Introduction

It is expected that the number of people with dementia will grow exponentially in the coming years; most of them will be cared for by family and other unpaid carers [1,2]. In Europe, families and other unpaid carers provide about 75% of the care or supervision for people with dementia living at home, including help with activities of daily living, finances, and arranging care such as scheduling appointments with professionals [3,4]. The provision of unpaid care often affects carers’ lives negatively. They are prone to feelings such as stress, depression, anxiety, and being overburdened when providing care for a prolonged period of time [5]. This is especially notorious in dementia where the person becomes increasingly dependent on care during the course of the disease [6].

Consequently, the World Health Organization (WHO) identified family members’ and other unpaid carers’ need of support as a key priority [4,7]. The Dutch government also framed the improvement of the quality of life of carers of people with dementia as a health priority. One of the objectives of the Dutch dementia strategy is to develop and implement new care models with effective tools and interventions for both people with dementia as well as their unpaid carers [8].

In recent years, several types of interventions have been developed to ameliorate the health and well-being of carers of people with dementia. Examples are psychoeducational programs, cognitive behavioral therapy (CBT), respite care, and occupational therapy [9]. Psychological treatments aimed at improving carers’ ability to cope with problematic behavior, to cope with stressful situations, to enhance communication with the person with dementia, and to ask for support from others have been demonstrated to be effective in improving carers’ mental health and well-being [10-12]. Despite the progress of psychological face-to-face interventions specifically designed for carers of people with dementia, most carers still do not use or are unable to access this professional support because they are unaware of its existence, they have time constraints, or they do not want psychological help (ie, negative attitude possibly reinforced by cultural influences) [7]. Online interventions may be an effective solution to overcome these accessibility barriers. Previous research has found promising results of online interventions even when compared to face-to-face interventions [13-18]. Unguided interventions are generally seen as less effective than those that are guided by a therapist or coach, whether online or by telephone [16]. However, unguided or minimally guided interventions have the advantage that they can be easily scaled up because no extensive input of a therapist is needed. Additionally, online interventions in any format are advantageous for people because they do not have to schedule specific appointments and they do not need to travel to any particular setting. Furthermore, online interventions might help reduce the stigma that still remains in society regarding dementia and receiving psychological support as a carer. Therefore, with the help of an international expert panel, the WHO has developed iSupport, an online knowledge and skills training program, which aims to improve carers’ mental health and coping resources. iSupport is based on psychoeducation and CBT techniques, such as activity scheduling, relaxation, and cognitive reframing. A first adaptation of iSupport has been carried out for India. A pilot study was carried out with the adapted English version in India from 2017 to 2018 [19]. For our study, we translated iSupport into Dutch and adapted the text in line with the WHO’s adaptation and implementation guide for the Netherlands.

Currently, families and other unpaid carers in the Netherlands can find information, training, and support through a wide variety of online internet resources. These resources include the following: informative websites (eg, dementie.nl, owned by the Alzheimer’s Association in the Netherlands); an online social support intervention [20]; free and paid apps to organize family care, organize other unpaid care, and increase peer support to improve communication between carers [21]; a self-guided, e-learning course with different levels of knowledge tailored to the needs of unpaid and professional dementia carers [18]; and a guided internet intervention to reduce psychological distress of caregivers of people with dementia with online coaching by a mental health professional [22,23].

iSupport is an addition to this broad spectrum of internet interventions. As an online training and support program with minimal guidance, iSupport focuses on mental health outcomes of family and other unpaid carers. The iSupport program is flexible (ie, carers can select the topics they prefer) and personalized (ie, provides automatically personalized feedback). This paper describes the design of a randomized controlled trial (RCT) to examine the effectiveness and usability of iSupport for family and other unpaid carers of people with dementia; we examined the tool’s ability to reduce carers’ distress and improve mental health (eg, depression and anxiety symptoms and caregiver burden) and to increase coping resources (eg, mastery, self-competence, and self-efficacy) compared to a waiting list control group.

## Methods

### Study Design

The study has been designed as a two-arm superiority RCT. Carers will be randomized to (1) the intervention group that will use iSupport, an online training and support program, or (2) a waiting list control group. The iSupport intervention group will be provided with access to the intervention for 3 months immediately following the randomization; those assigned to the control group will receive access to iSupport 3 months after randomization (see Figure 1). The study will be carried out according to the Consolidation Standards of Reporting Trials (CONSORT) guidelines [24].

**Figure 1 figure1:**
[figure not shown]
Consolidation Standards of Reporting Trials (CONSORT) diagram for this study.

### Inclusion and Exclusion Criteria

The potential participants will be relatives or other unpaid carers of people with dementia. The participants must be at least 18 years old. We will focus on unpaid carers who are providing care to a family member, friend, or neighbor for at least 6 months, regardless of the number of hours per day they spend on care provision. To be included in the study, their well-being will need to have been affected at least to some extent. We will measure well-being via levels of stress, existence of depressive or anxiety symptoms, or experience of caregiver burden. This means that the carers will need to have a score greater than 13 on the Perceived Stress Scale (PSS) [25], a score of 4 or greater on the Hospital Anxiety and Depression Scale-Anxiety subscale (HADS-A) [26], or a score of 4 or greater on the Centre for Epidemiological Studies Depression scale (CES-D) [27]. Caregiver burden will be assessed using a one-item scale with a score ranging from 1 (no burden) to 10 (extreme burden); people will be eligible for the study if they scored 4 or greater.

Furthermore, there needs to be an indication that the person that is being cared for is indeed living with dementia. Therefore, carers will have to fill out the Ascertain Dementia 8-item informant questionnaire (AD8) [28]. The AD8 assesses the functional decline of the person with dementia attributed to cognitive impairment over the past years as reported by the carer. In order to be included, the score needs to be 2 or higher. This cutoff has been shown to have a good discriminative validity between people with and without dementia. We will also ask whether or not the person has been officially diagnosed with dementia, but this will not serve as an inclusion criterion.

We will exclude people who are unable to comprehend written Dutch or have no access to the internet. If both groups differ regarding the professional support they have received, we can control for it in the analyses, but receiving professional support will be not be used as an exclusion criterion.

### Recruitment of Participants and Study Procedure

People will be recruited through different sources. First, Alzheimer Nederland (AN), the Dutch Alzheimer’s national association, will place announcements about the study on their website, social media pages, and newsletter, among other places. Second, study banners will be placed on other relevant websites. Third, the research team will leave brochures and posters while visiting Alzheimer’s cafés and memory clinics. All of our study announcements will refer to our study website [29], which contains information about the study purpose and procedures. Those who are interested in participating will be able to register through this study website. We will then contact them via email where we will include a brochure with the information and a link to the online battery of baseline questionnaires, which includes the screening questions and the online written informed consent form. At this stage, we will fully inform potential participants about the aim and procedures of the study and will again ask for online informed consent. Based on the answers to the screening questions from the battery of baseline questionnaires, we will check the inclusion and exclusion criteria. Those who do not fulfil our inclusion criteria or do not provide informed consent will not be able to continue to fill out the remainder questionnaires of the baseline battery. They will receive an automated message explaining why they cannot participate in the study. We will stress that they can consult their general practitioner and AN at any time. Those who fill out the full battery of baseline questionnaires and fulfil the inclusion criteria will be included in the study and will be randomized. The outcome of the randomization will be communicated to participants via email. Participants randomized to the iSupport group will receive the intervention log-in details and they will have access to the intervention for 3 months. After the third month, participants will no longer have access to the intervention. Those who are randomized to the waiting list control group will be informed that they will receive log-in details for iSupport after they have completed the 3-month assessment. They will be free to seek any help they want in the meantime. The postintervention measurement and follow-up measurement will be sent via email 3 months and 6 months after randomization, respectively.

### Ethical Approval

The trial will be conducted according to Dutch and European legal requirements and standards as well as the Declaration of Helsinki (World Medical Association, 2013). The study protocol was reviewed by the Ethical Committee of the Faculty of Behaviour and Movement Sciences of the Vrije Universiteit Amsterdam (approval number: VCWE-2017-126); according to the review by the Medical Research Ethical Committee of the Vrije Universiteit medical center, this study does not fall within the scope of the Medical Research with Human Beings Act (review number: 2017.331).

### Randomization and Blinding

A randomization schedule with a 1:1 allocation ratio will be made with a computerized random number generator using variable block sizes of two and four by an independent researcher. We will stratify for gender and for the type of relationship between the carer and the person with dementia (ie, partner or other). After every inclusion, the same independent researcher will reveal the next randomization outcome so that allocation is concealed. Participants will be informed about the randomization outcome by email.

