### Sample Size

Perceived stress is our primary outcome measure and is used for the power calculation. Based on the results of a previous study about an online intervention for carers [39], we expect an effect size (Cohen *d*) of 0.40. Assuming an alpha of .05 and a statistical power (1-beta) of .80 in a two-tailed test, we will need 100 respondents in each of the conditions, resulting in a total of 200 participants. Calculation of the sample size was carried out with G*Power 3.1.9.2 (Heinrich-Heine-Universität Düsseldorf) [40].

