### Statistical Analysis

We will first check whether or not the randomization was successful by comparing the two groups for all baseline variables with *t* tests for continuous data or chi-square tests for dichotomous data. We will also check for differences between study dropouts and those who remain in the study at 3 months. The primary analyses will be based on the intention-to-treat principle. Sensitivity analyses will be performed only with those participants that filled out the pre- and posttest questionnaires (ie, completers). Missing data handling will depend on the amount and pattern of missing data, selecting the most appropriate technique. We will use the generalized estimating equation to examine the association between changes in stress scores (ie, PSS scores) and treatment arms (ie, iSupport vs waiting list). We will correct for baseline scores if they are not equally distributed. We will examine the influence of age, gender, and relationship (ie, spouses vs other relationship) on the outcomes. These analyses will be repeated for burden, anxiety and depression, sense of competence, self-efficacy, and mastery. Next, we will express the between-group, posttest, effect sizes for the different outcomes using Cohen *d*. Cohen *d* is the difference between the two posttest means divided by the pooled standard deviation. An effect size of 0.8 is considered to be large, an effect size of 0.5 is considered to be moderate, and an effect size of 0.2 is considered to be small.

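### Randomisation is stratified by gender and relationship, but the article does not commit to putting these strata in the primary model and words the relationship grouping differently; the cost is a small loss of precision

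*Protocol article*

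**What the plan says.** **Design.** The Randomization and Blinding section states: "A randomization schedule with a 1:1 allocation ratio will be made with a computerized random number generator using variable block sizes of two and four". It then names two stratification factors: "We will stratify for gender and for the type of relationship between the carer and the person with dementia (ie, partner or other").

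**Analysis.** Three sentences of the Statistical Analysis section bear on the primary model:

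- The model: "We will use the generalized estimating equation to examine the association between changes in stress scores (ie, PSS scores) and treatment arms".
- Baseline adjustment: "We will correct for baseline scores if they are not equally distributed".
- Gender and relationship: "We will examine the influence of age, gender, and relationship (ie, spouses vs other relationship) on the outcomes".

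The section then says that these analyses are repeated for burden, anxiety and depression, sense of competence, self-efficacy and mastery.

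**Sample size.** The Sample Size section says "we expect an effect size (Cohen *d*) of 0.40" and "we will need 100 respondents in each of the conditions, resulting in a total of 200 participants".

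**The concern.** Stratified blocking balances the arms within each combination of gender and relationship. Outcome differences between strata therefore add almost nothing to the variability of the treatment contrast. A model with treatment arm alone still counts those differences as residual noise. Its standard error is then larger than the true sampling variability, its confidence interval is too wide and its test rejects too rarely under the null. The precision that stratification provides is not used.

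The article does not say that the strata enter the treatment-effect model. They are listed together with age, which is not a stratification factor, as variables whose influence is of interest. That could mean covariates, predictors or moderators.

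The relationship grouping is also glossed in two ways: partner versus other at randomisation, spouse versus other in the analysis. An unmarried partner belongs to the partner stratum but could be analysed as other. Leaving the role open would also allow a choice between adjusted and unadjusted results after the data are seen.

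**Working it through.** **1. The plan's own figure.** Inputs from Sample Size: d = 0.40, two-sided alpha 0.05, power 0.80. With SD = 1, n per arm = 2 × ((1.96 + 0.842)/0.40)² = 98.1, so 99. The exact t-test gives 99.08, so 100 per arm, as stated. At 100 per arm, z = 0.40 × √(100/2) = 2.83. Power is 0.807 by the normal approximation and 0.804 by the t-test.

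**2. Assumption.** Let R2 be the share of outcome variance that the four strata explain. The article gives no value, so 0.01 to 0.10 is shown.

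**3. Formulas** (normal approximation, 100 per arm, total SD 1, s = √(1 − R2)):

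- Unadjusted SE relative to the correct SE: 1/s
- True size of the unadjusted test: 2 × (1 − Φ(1.96/s))
- Power, strata left out: Φ((2.83 − 1.96)/s)
- Power, strata in the model: Φ(2.83/s − 1.96)

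| R2 | SE too wide by | Size, strata out | Power, strata out | Power, strata in | Gain over strata out (points) | Gain over 0.807 (points) |
|---|---|---|---|---|---|---|
| 0.01 | 0.5% | 0.049 | 0.809 | 0.811 | 0.3 | 0.4 |
| 0.02 | 1.0% | 0.048 | 0.810 | 0.815 | 0.5 | 0.8 |
| 0.05 | 2.6% | 0.044 | 0.814 | 0.827 | 1.3 | 2.0 |
| 0.10 | 5.4% | 0.039 | 0.820 | 0.846 | 2.6 | 3.9 |

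The last two columns use different reference points. The first compares the two analyses of the same stratified trial. The second compares the adjusted analysis with the planning figure, which ignores the strata. Together they give the range of 1 to 2 points at R2 = 0.05 and 3 to 4 points at R2 = 0.10. At R2 of 0.01 to 0.02 the larger of the two is 0.4 to 0.8 points.

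**4. Simulation.** Permuted blocks of 2 and 4 in four strata, N = 200, 4,000 runs per setting, linear model with and without strata:

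- R2 = 0.05: mean unadjusted SE 0.141 against a true sampling SD of 0.136; type I error 4.5% unadjusted, 5.0% adjusted; power 81.3% against 82.9%.
- R2 = 0.10: type I error 4.1% against 5.1%; power 81.7% against 84.5%.
- R2 = 0.01: power 79.4% against 79.8%. The Monte Carlo standard error of each power figure is about √(0.8 × 0.2/4000) = 0.6 points, so the level is noisy, but the two analyses are practically the same.

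**5. Robust standard errors.** A GEE normally uses the sandwich estimator. Repeating the simulation with it (6,000 runs per setting) did not remove the effect. At R2 = 0.10 the unadjusted SE was 0.141 against a true SD of 0.134, size was 4.0%, and power was 82.8% against 85.6% adjusted. At R2 = 0.05 power was 82.1% against 83.9%.

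All these figures treat the comparison as one outcome per participant, as the sample-size calculation does.

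**The case against.** **The strata may be in the model.** A reader might infer that the plan omits the strata from the primary analysis. The text does not support that. Both factors are named in the analysis paragraph, and examining their influence can be read as covariate adjustment. This objection stands: the supportable point is an open role, not an exclusion.

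**An article leaves the covariate list to an analysis plan.** This is partly right, and it keeps the point small. But the article does state the model, a rule for baseline adjustment and a use for these two variables. An unseen plan also does not resolve the two wordings of the relationship grouping, although these may be loose glosses on one variable and nothing shows that two codings will be used.

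**The size rests on an assumed R2.** This stands. The article models changes in stress. A stable difference in stress level between, say, partners and others would largely cancel in a change score or be partly absorbed by baseline correction. The relevant R2 could then be well below 0.05.

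**The error is on the safe side.** This stands too. A reader might infer that wide standard errors make the trial underpowered or its result unreliable. Neither follows: type I error stays at or below 5%, the treatment estimate is not biased, and calculated power exceeds 0.80 without the strata when 100 per arm are analysed.

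**Conclusion.** The point holds as a free improvement and a wording conflict to reconcile, not as an error that threatens the result. The sentence defining the primary GEE names only treatment arm, nothing commits the trial to analysing by the strata it randomises by, and relationship is described in two ways.

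If the strata are left out, the standard error is too wide by 0.5% to 5.4% and the true size is 0.049 to 0.039 for R2 of 0.01 to 0.10. The power forgone is under one point at R2 of 0.01 to 0.02, 1 to 2 points at 0.05 and 3 to 4 points at 0.10. These figures assume d = 0.40, 100 analysed per arm and the stated R2, and could be smaller for change scores. The possible misclassification of unmarried partners cannot be sized, because the article does not say how many there will be.

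**What to change.** Add one sentence to Statistical Analysis: gender and relationship (partner versus other, coded exactly as at randomisation) are fixed covariates in the primary GEE and in all secondary-outcome models, whatever their observed influence. Replace the spouse grouping with the randomisation grouping. If it matters whether the effect differs by gender, relationship or age, describe that as a separate exploratory analysis of arm-by-factor interactions.

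The cost is the wording alone. Gender and relationship are needed to randomise each participant and are among the baseline sociodemographic data, so there is nothing further to collect and the sample size does not change.
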